**Fig. 2 Fig2:**
[figure not shown]
Examples of crafts to be performed by participants in the Intervention group: **a** air dry clay art, **b** quilling, **c** batik painting, **d** origami, **e** threading beads, **f** card making, **g** cloth stamping, **h** wooden frame design, **i** sewing, **j** Perler beading, **k** braiding and cup mat, and **l** soap making

### Criteria for discontinuing or modifying allocated interventions {11b}

Given some of the participants may show different rates of improvement and recovery after surgery, each craft will be graded and modified according to the participant’s hand dominance and his/her ability to use the injured hand. The Researcher will take precautions in selecting safe materials and activities, yet some participants may need assistance with sharp tools such as scissors.

### Strategies to improve adherence to interventions {11c}

The Researcher will track participant attendance to ensure all therapy sessions are completed before Therapist B does the final assessment. If a participant fails to attend a session, the Researcher will phone the participant to reschedule within the timeframe of the study.

### Relevant concomitant care permitted or prohibited during the trial {11d}

Participants will be allowed to consume any prescribed medication, including analgesics, during the study. If, however, analgesic consumption exceeds more than that prescribed while participating, this will be documented by Therapist A and the Researcher. Participants will be excluded if other Occupational therapy or Physiotherapy for the injured hand is initiated while participating in this 6-week study. During the study, Intervention group participants will be allowed to replicate the protocol craft-making activities at home.

#### Provision for post-trial care {30}

Participants in both the Control and Intervention groups will be allowed to continue therapy as necessary after completing the 6-week study.

#### Outcomes {12}

The primary outcome implemented in this study is the Quick-DASH (Disabilities of the Arm, Shoulder and Hand) to assess upper limb disability. The secondary outcomes include the Patient Rated Wrist Evaluation (PRWE), which is specific for evaluating wrist disability and the Impact of Event Scale-Revised (IES-R) for rating post-traumatic stress. Additional secondary outcomes include components of physical performance (measured by)—dexterity (Purdue Pegboard Test), AROM of forearm, wrist and fingers (goniometer), and grip strength (Jamar™ dynamometer).

### Participant timeline {13}

Participants will be required to attend therapy twice weekly for 6 weeks for a total of 12 therapy sessions. The enrollment, intervention, and assessment began in July 2021 and was expected to end in December 2023 (Table 4).

**Table 4 Tab4:**
[figure not shown]
Schedule of enrollment, interventions, and assessments

#### Sample size {14}

In regard to the primary outcome of this study, the sample size required was calculated with a G* power sample size calculator. Analysis was done using ANOVA repeated measures, within-between interaction in *F* tests family. A priori type of power analysis was used to compute the required sample size. Analysis was done with Cohen-f effect size at 0.25 for a medium effect, alpha error at 0.05, and 80% power. There are two groups (Control and Intervention) with two sets of measurements (initial baseline and final) to be compared. Correlation among repeated measure was set at 0.5 and the non-sphericity correction was 1.0. The result of priori analysis indicates a total of 34 participants will be needed; however, a 10% dropout rate (4 participants) is anticipated bringing the total sample size required to 38 participants.

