### Outcome measures

#### Quick-Disabilities of the Arm, Shoulder and Hand (DASH)

The Quick-DASH is a shortened version of the original DASH, and both versions are self-report questionnaires [20]. The Quick-DASH has 11 items that are useful for assessing physical function, symptoms, and quality of life in people with upper limb musculoskeletal disorders. The calculated score for the Quick-DASH, using the formula below, ranges between 0 and 100 with a higher score an indication of greater disability [21, 22]. The minimal clinically important difference for Quick-DASH is 12.85 at 90% confidence level [23].

Quick DASH score formula:$$\mathrm{Total\ score}=\left(\left[\frac{\mathrm{sum\ of\ }n\mathrm{\ responses}}{n}\right]-1\right)\times 25$$

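### The effect size labelled medium in the sample size section is a 1.0-SD difference in Quick-DASH change in this design; power for 0.5 SD is about 29%

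*Protocol article*

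**What the plan says.** The Sample size section of the protocol article sets out the calculation for the primary outcome, the Quick-DASH. The procedure is given as "Analysis was done using ANOVA repeated measures, within-between interaction in" the F tests family of G*Power. The effect size is stated as "Analysis was done with Cohen-f effect size at 0.25 for a medium effect, alpha error at 0.05, and 80% power". The layout is described as "There are two groups (Control and Intervention) with two sets of measurements (initial baseline and final) to be compared", and "Correlation among repeated measure was set at 0.5 and the non-sphericity correction was 1.0". The outcome is "The result of priori analysis indicates a total of 34 participants will be needed", after which "a 10% dropout rate (4 participants) is anticipated bringing the total sample size required to 38 participants".

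The section does not express f in SD units or Quick-DASH points, and the article gives no Quick-DASH SD. The Quick-DASH paragraph under Outcome measures says "The minimal clinically important difference for Quick-DASH is 12.85 at 90% confidence level"; the sample size calculation does not use that figure. The primary analysis, under Statistical methods for primary and secondary outcomes, is a mixed model ANOVA of Quick-DASH at baseline and after the 12th session, which matches the test that was powered.

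**The concern.** The value f = 0.25 is the usual medium benchmark for comparing group means. With two groups, f = d/2 there, so it corresponds to a difference of 0.5 SD. The same f entered in a 2×2 within-between interaction describes a different and larger treatment effect. The treatment effect of interest is the difference between groups in Quick-DASH change. A reader who sees 80% power and a medium effect will take it that a moderate difference of that kind is covered.

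At stake is how the result is read. The intervention adds about 15 minutes of craft to a 1-hour session, and the Discussion part of the Abstract says the trial is meant to establish whether crafts have value. If the trial can reliably detect only a difference near one full SD, a non-significant result says little about moderate benefits, and the power statement should not suggest otherwise.

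**Working it through.** **Inputs (Sample size section).** f = 0.25; alpha = 0.05; target power 80%; k = 2 groups; m = 2 measurements; rho = 0.5; non-sphericity correction 1.0. I assume equal groups, as the G*Power calculation does.

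**Step 1: reproduce the plan's figure.** For this G*Power procedure, with epsilon the non-sphericity correction:

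- lambda = f² × N × m × epsilon / (1 − rho)
- numerator df = (k − 1)(m − 1) = 1; denominator df = (N − k)(m − 1) = N − 2

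With N = 34: lambda = 0.0625 × 34 × 2 / 0.5 = 8.5. The noncentral F distribution on 1 and 32 df gives power 80.7%. With N = 32, lambda = 8.0 and power is 78.1%. The smallest even N is therefore 34, as stated. Dropout: 34 / 0.90 = 37.8, rounded up to 38, as stated. The match confirms which definition of f was used.

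**Step 2: what f = 0.25 means here.** Take cell means in SD units of 0 and 0 for Control (baseline, final) and 0 and 1 for Intervention.

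- Row means are 0 and 0.5; column means are 0 and 0.5; the grand mean is 0.25.
- Interaction effect = cell − row mean − column mean + grand mean. The four values are 0.25, −0.25, −0.25 and 0.25.
- f is the root mean square of these values, 0.25.

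The difference between groups in change is (1 − 0) − (0 − 0) = 1.0 SD. In general it is 4f SD.

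The SD of change is SD × √(2(1 − rho)). At rho = 0.5 this equals the single-score SD, so the effect is d = 1.0 on either scale. As a cross-check, a two-sample t test on change scores with d = 1.0 and 17 per group also gives 80.7%, and a simulation of 40,000 trials gave 80.5%.

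**Step 3: power for other differences in change (rho = 0.5).**

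| Difference in change | f = d/4 | Power, 34 (17/17) | Power, 38 (19/19) |
|---|---|---|---|
| 1.0 SD | 0.25 | 80.7% | 85.1% |
| 0.8 SD | 0.20 | 61.9% | 67.0% |
| 0.5 SD | 0.125 | 29.3% | 32.3% |

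For 0.5 SD at N = 34, lambda = 0.015625 × 34 × 2 / 0.5 = 2.125; simulation gave 29.6%. Power first reaches 80% at N = 128 (64 per group, lambda = 8.0, power 80.1%). With 10% dropout that is 128 / 0.90 = 142.2, rounded up to 143.

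**Step 4: sensitivity to the correlation.** For a difference of 0.5 single-score SD at 17 per group, power is 22% at rho 0.3, 29% at 0.5, 45% at 0.7, 61% at 0.8 and 89% at 0.9.

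**Step 5: the 12.85-point MCID.** Power depends on d = 12.85 / [SD × √(2(1 − rho))]. The SDs below are my assumptions, since the article gives none; 17 per group.

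| Assumed SD | rho 0.5 | rho 0.8 |
|---|---|---|
| 12.85 | 81% | 99% |
| 15 | 68% | 97% |
| 20 | 44% | 82% |
| 25 | 31% | 63% |

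**Step 6: sensitivity to group sizes.** The Sequence generation section fixes no allocation ratio. For 1.0 SD and 34 analysed, power is 80.7% at 17/17, 78% at 13/21 and 77% at 12/22.

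**The case against.** The strongest defence is that nothing is miscalculated. The section claims 80% power for f = 0.25, and the design has it. Medium is the customary name for that value on the f scale, and the article never mentions d or 0.5 SD. All of this stands, so a reader should not infer an arithmetic error. It does not rescue the label. The label describes the treatment effect on the primary outcome, and the section gives no SD or point equivalent from which a reader could see that the effect is 1.0 SD.

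A higher true correlation would help. For 0.5 SD, however, power passes 80% only at very high values (61% at 0.8, 89% at 0.9), and the plan itself sets 0.5.

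Two stronger readings are tempting and not supported. One is that the trial is underpowered for the MCID. With no SD stated, that cannot be settled: power for 12.85 points runs from 31% to well above 80% over plausible-looking combinations of SD and correlation. Nor does the article present 12.85 as a design target; it appears in the description of the instrument. The other is that the investigators will read a null result as proof that craft adds nothing. The article does not say so. The risk lies in what the power statement invites.

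It might also be said that a baseline-adjusted ANCOVA would make up the shortfall. At rho 0.5 it raises power for 0.5 SD only to about 37%.

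**Conclusion.** The point holds as a fault of labelling. The sample size of 34 (38 with dropout) is right for its inputs, but the effect it was computed for is a 1.0-SD between-group difference in Quick-DASH change, conventionally a large effect. For a conventional medium difference of 0.5 SD, power is about 29% with 34 analysed and 32% with 38, against the 80% that the wording suggests; 80% would take 128 analysed.

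These figures rest on the plan's correlation of 0.5, on groups of equal size, and on taking medium to mean 0.5 SD. Unequal groups would lower power slightly. No firm power for 12.85 points can be given from the article.

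**What to change.** Keep 38 participants. In the Sample size section, delete the description of the effect as medium and replace the power statement with wording such as:

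> Assuming a correlation of 0.5 and about 17 per group, 34 evaluable participants give about 81% power for a 1.0-SD between-group difference in Quick-DASH change, 62% for 0.8 SD and 29% for 0.5 SD. Power is slightly lower if the groups are unequal.

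Add that a non-significant result will be interpreted through the 95% confidence interval for the difference in change, set against the 12.85-point MCID, and not as absence of effect. If power for 12.85 points is quoted, show it over a range of both assumed SD and correlation, as in Step 5, and label the SDs as assumptions.

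The change is to wording only: recruitment and the planned test stay as they are. The price is that the stated power becomes less favourable.

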### Recruitment {15}

All patients with lower-third forearm fractures stabilized by ORIF, who are referred to Occupational Therapy between 2–4 weeks after ORIF and meet the inclusion criteria will be recruited.

## Assignment of intervention: allocation

### Sequence generation {16a}

Group allocation will be done using a random draw method requiring the participant to draw from a large envelope holding two smaller opaque-sealed envelopes each containing a different group assignment. This study will not use an allocation ratio.

### Concealment mechanism {16b}

There will be a large envelope with two opaque-sealed envelopes containing a slip of paper labeled as either Control or Intervention group. The larger envelope will be presented to each participant with instruction to randomly pick a sealed envelope.

### Implementation {16c}

Randomization is done by the Researcher on the initial therapy visit.

## Assignment of intervention: blinding

### Who will be blinded {17a}

Therapist A and Therapist B will be blinded to the participant’s group allocation. The Researcher will not be blinded as the Researcher will be involved in the craft-making sessions. Similarly, the participants once assigned to a group will no longer be blinded to the other group’s intervention. To ensure that Therapist A and Therapist B remain blinded over the 6-week study, the Researcher will continually remind each participant not to reveal his/her group allocation to Therapist A or B.

### Procedure for unblinding if needed {17b}

There is no known circumstance or procedure that would require revealing a participant’s allocation.

## Data collection and management

### Plans for assessment and collection of outcomes {18a}

Prior to the first therapy session, Therapist B will do the initial baseline assessment. During the assessment, each participant will be interviewed by Therapist B to obtain his/her demographic data and pertinent medical history. After obtaining this information, the outcome assessments related to disability, physical performance, and post-traumatic stress will be done. Therapist B will also do the 6-week reassessment after completion of the 12th therapy session.

### Outcome measures

#### Quick-Disabilities of the Arm, Shoulder and Hand (DASH)

The Quick-DASH is a shortened version of the original DASH, and both versions are self-report questionnaires [20]. The Quick-DASH has 11 items that are useful for assessing physical function, symptoms, and quality of life in people with upper limb musculoskeletal disorders. The calculated score for the Quick-DASH, using the formula below, ranges between 0 and 100 with a higher score an indication of greater disability [21, 22]. The minimal clinically important difference for Quick-DASH is 12.85 at 90% confidence level [23].

Quick DASH score formula:$$\mathrm{Total\ score}=\left(\left[\frac{\mathrm{sum\ of\ }n\mathrm{\ responses}}{n}\right]-1\right)\times 25$$

#### Patient-Rated Wrist Evaluation (PRWE)

The PRWE is a self-report questionnaire designed to measure wrist pain and disability experienced during activities of daily living after wrist injury. The PRWE has 15 items that are divided into two subscales: pain (5 items) and function (10 items) [20]. The total score is calculated using a provided formula with a higher score an indication of greater disability [22, 24]. The minimal clinically important difference for PRWE for patient with distal radius fractures is 11.5 points for a 95% confidence level [25].

#### Impact of Event Scale-Revised (IES-R)

The IES-R is also a self-report questionnaire used to assess a person’s response to traumatic events. The IES-R has 22 items divided into three subscales: intrusion, avoidance, and hyperarousal. The IES-R measures the frequency of symptoms occurrence over the past week. The results of the subscales are added for a total score that can range between 0 and 88 with a higher score an indication of more post-traumatic stress [26, 27].

#### Purdue Pegboard Test (PPT)

The PPT is a performance-based assessment for measuring fine and gross motor dexterity of the hand and fingers. There are five subtests: (1) Right hand, (2) Left hand, (3) Both hand, (4) Total of Right hand + Left hand + Both hand (not an actual test but a summation of scores of the first three subtests), and (5) Assembly. Each subtest will be performed by the participant three times and the average score calculated. The validity coefficients of the PPT ranges between 0.70 and 0.76 depending on the demographic characteristics of the participant [28].

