#### Dynamometry

Grip strength will be measured using a Jamar™ dynamometer with the handle position set on the second notch while the participant is seated with his/her elbow flexed to 90° and stabilized beside the side of the body as recommended by the American Society of Hand Therapists [30]. Therapist B will ask the participant to squeeze the handle as hard as he/she can for 3 s while the reading is being obtained. The grip strength test will be performed three times beginning with the non-affected hand then alternating to the affected hand. Participants will be advised not to exceed their comfort level and not to cause pain when squeezing with their affected hand. For participants who are not able to generate any force with their affected hand, 0 kg will be recorded. The grip strength score is the average of three trials for each hand recorded in kilograms.

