## Statistical methods

### Statistical methods for primary and secondary outcomes {20a}

All data will be analyzed using the IBM Statistical Product and Service Solutions (IBM SPSS). Descriptive analysis for categorical data such as gender, marital status, hand dominance, type of wrist fracture, and educational level will be expressed in frequency, percentage, and proportion. Descriptive statistics will be used to analyze continuous data including age, Quick-DASH score, PRWE score, IES-R score, PPT score, AROM of the forearm and wrist, TAM for the digits, and grip strength. These results will be expressed as mean, standard deviation, minimum and maximum if the data is normally distributed or as median and interquartile range. If the data is not normally distributed, sub-analysis will be conducted to determine the outlier and the outlier will be extracted from the data set if it shows significant influence. A mixed model ANOVA will be used to test the primary outcome of this study by evaluating the mean difference between and within groups of the Quick-DASH scores obtained at baseline and after the 12th therapy session. The difference in the initial and final PRWE score, IES-R score, PPT score, AROM of the forearm and wrist, and TAM of the digits and grip strength will be analyzed using a mixed model ANOVA. Depending on the results of the aforementioned analyses, other sub-analysis will be performed as necessary.

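### The single-hand Purdue Pegboard scores are defined by right and left rather than by injured side; compared as defined, they would pool injured and uninjured hands and attenuate any effect.

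*Protocol article*

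**What the plan says.** Under Outcomes {12}, the physical-performance secondary outcomes are "dexterity (Purdue Pegboard Test), AROM of forearm, wrist and fingers (goniometer), and grip strength". Under Outcome measures, the PPT section states "There are five subtests: (1) Right hand, (2) Left hand, (3) Both hand"; the remaining two scores are a Total, which sums those three, and Assembly. It adds: "Each subtest will be performed by the participant three times and the average score calculated". No PPT score is linked to the injured hand.

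The section on statistical methods {20a} applies a mixed model ANOVA to "The difference in the initial and final PRWE score, IES-R score, PPT score, AROM of the forearm and wrist" and the remaining measures. It does not say which of the five PPT scores is meant, or which hand.

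The Dynamometry section does use injury side: "The grip strength test will be performed three times beginning with the non-affected hand then alternating to the affected hand".

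Eligibility criteria {10} do not restrict the injured side or the dominant hand, and they exclude fractures of multiple limbs. Table 3 gives separate dominant-hand and non-dominant-hand instructions for batik painting, and section {11b} grades each craft by hand dominance and use of the injured hand. The protocol therefore expects injuries on both sides, with essentially one injured hand per participant.

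**The concern.** A right-hand mean taken across all participants averages two kinds of hand: injured hands, which are recovering and on which craft might act, and healthy hands, for which little treatment effect is expected. A left-hand mean does the same with the roles reversed. The between-group difference on either score is then a weighted average of the effect on injured hands and the effect on healthy ones.

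This matters because fine motor control is one of the protocol's stated reasons for using craft (Background and Table 2), and dexterity is part of the third hypothesis. The Quick-DASH, PRWE and IES-R are self-reports from participants who know their allocation. The PPT is a performance test given by a therapist who is meant to be blinded, so it is useful corroboration. An avoidable loss of sensitivity there is worth removing.

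**Working it through.** **Reproducing the protocol's own figure.** Sample size {14} gives f = 0.25, alpha 0.05, 80% power, two groups, m = 2 measurements, correlation 0.5 and non-sphericity correction 1.0. For the within-between interaction, the noncentrality is lambda = f² × N × m / (1 − rho), with 1 and N − 2 degrees of freedom.

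- N = 34: lambda = 0.0625 × 34 × 2 / 0.5 = 8.5, power 80.7%. N = 32 gives 78.1%, so 34 is reproduced.
- 34 / 0.9 = 37.8, rounded up to 38, also reproduced.

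With two time points this test is equivalent to a two-sample t-test on change scores, where lambda = N × d² / 4. Hence d² = 4 × 8.5 / 34 = 1, that is, 1.0 SD of change. The calculation is for the Quick-DASH; the document gives no effect size for the PPT. Using d = 1.0 for the injured hand is an assumption made only to put the loss on a familiar scale.

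**Retained share of the effect.** Let p be the share of participants injured on the right, and s the effect on the uninjured hand as a fraction of the effect on the injured hand. The document gives neither.

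- Right-hand score: p + (1 − p)s
- Left-hand score: (1 − p) + ps

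The two shares add to 1 + s whatever the value of p. Power below is for N = 34 with d = 1.0 on the injured hand and the SD held at 1.

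| p | s | Right: share, power | Left: share, power |
|---|---|---|---|
| 0.3 | 0 | 0.30, 13.6% | 0.70, 50.8% |
| 0.5 | 0 | 0.50, 29.3% | 0.50, 29.3% |
| 0.5 | 0.25 | 0.625, 42.4% | 0.625, 42.4% |
| 0.5 | 0.5 | 0.75, 56.4% | 0.75, 56.4% |
| 0.7 | 0 | 0.70, 50.8% | 0.30, 13.6% |
| 0.7 | 0.5 | 0.85, 67.1% | 0.65, 45.2% |

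The affected-hand score keeps the whole effect, with power 80.7%. Over p from 0.3 to 0.7 and s from 0 to 0.5, the retained share runs from 0.30 to 0.85. Both scores stand at one half together only when p = 0.5 and s = 0; about 128 participants would then be needed for 80% power.

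**Added variance.** If injured hands also change more than uninjured hands in both arms, by g SD, mixing adds p(1 − p)g² to the variance. At p = 0.5 and s = 0, the standardised effect is 0.5 / √1.25 = 0.45 of its affected-hand value for g = 1, and 0.5 / √2 = 0.35 for g = 2. The values of g are assumed.

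**The other three scores.** Both-hand and Assembly are not split by side, so there is no mixing. For the Total, write δ for the effect on the injured hand and δ_B for the effect on Both-hand. The raw effect is δ + sδ + δ_B, which does not contain p. The uninjured hand adds mainly noise to the Total.

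**The case against.** The strongest reply is that the PPT section describes how the instrument is administered, not which comparisons will be made. The analysis text says only PPT score. Nothing states that the right-hand and left-hand means will be tested, and nothing rules out recoding by injured side. Such detail often sits in an analysis plan, and none is shown here. The grip section suggests that the authors do think in terms of the affected hand. This stands in part: the attenuation is conditional on the scores being used as listed. It does not dispose of the point, because the listed scores are the only PPT definitions given, and following them gives a worse comparison than a simple recode would.

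A reader might infer that the dexterity outcome as a whole loses about half its effect, or that the PPT will mostly miss a real benefit. The documents do not support either. Side mixing concerns two of the five scores. One half requires assumptions about the side split and the uninjured hand that the article does not give, and no effect on the uninjured hand is not self-evident, since crafts such as origami, threading, sewing and braiding appear to use both hands. At a retained share of 0.75, power is 56%.

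It is also fair to say that grip and AROM are likewise measured by the same therapist, so the PPT is not the only check on the self-reports.

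**Conclusion.** The point holds in conditional form. The single-hand PPT scores are defined by right and left, the analysis does not map them to injury side, and either side may be injured. If those scores are compared as defined, each pools injured and uninjured hands and attenuates any effect on the injured hand.

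The size depends on assumed values of p, s and the PPT effect. There is some loss everywhere in the range examined; the fall in power from 81% to 29% is one illustration within it, not an estimate for this trial. The PPT is a secondary outcome, so neither the Quick-DASH analysis nor the planned 34 (38 with dropout) is touched. The change is still worth making, because it is free and improves the comparison whatever the side split.

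**What to change.** Before analysis, use the recorded injury side to recode the stored single-hand PPT scores as affected hand and unaffected hand. Name the affected-hand score as the one that carries the dexterity hypothesis; its baseline may be used as a covariate. Report the unaffected-hand, Both-hand, Total and Assembly scores as supportive. Write the rule down before group comparisons are seen.

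The cost is a recode of data already collected and a sentence or two in the analysis text. It needs no new measurement, visit or participant.
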